### Hypothesis

1)The 650 ILA group will have a significantly higher proportion of responders than the control group at 3 days after the end of intervention.2)The 650 nm ILA will show improvements in pain intensity, quality of life, and functional limitation in patients with NSCLBP.3)The 650 nm ILA would be a safe treatment for patients with NSCLBP.

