### Adverse events

Adverse events (AEs) are unintentional and undesirable symptoms, signs, or diseases that appear during or after treatment in a clinical trial. In our pilot study, no AEs and SAEs were associated with laser irradiation (21). AEs that could occur in our trial include bleeding, pallor, local hematoma, skin irritation, objective worsening of pain, and dizziness or fainting. All the AEs and SAEs would be recorded in detail, including the potential causalities between the intervention and AE, degree of severity, time of occurrence, and any measures taken to improve AE by the CRC. They will be reported to the IRB. The occurrence rate of SAEs and AEs will be compared between the two groups in the safety assessment. Participants who will experience AEs and SAEs related to our intervention will be compensated according to the relevant regulations.

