### Sample size estimation

In our previous pilot study (21), the difference in proportion of responders between 650 ILA (93% [14/15]) and control groups (40% [6/15]) was 53%. To obtain sufficient clinical data, we determined the sample size assuming an expected responder proportion of 30% in the control group and 60% in the 650 ILA group, a two-sided alpha level of 0.05, and a statistical power of 0.8. Under these assumptions, a total of 84 (42 per group) participants will be required. Estimating a maximum dropout rate of 20%, 106 participants (53 in each group) will be required in our trial.

$$\frac{n={\left(z_{\alpha /2}\,\sqrt{2\,\bar{p}\,\bar{q}}+z_{\beta }\,\sqrt{p_{1}\,q_{1}+p_{2}\,q_{2}}\right)}^{2}}{{\left(p_{t}-p_{c}\right)}^{2}}=\frac{{\left(1.96\,\sqrt{2\times 0.45\times 0.55}+0.842\,\sqrt{0.30\times 0.70+0.60\times 0.40}\right)}^{2}}{{\left(0.60-0.30\right)}^{2}}\approx 42$$

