### Statistical analysis

The final data will be analyzed by a biostatistician not involved in the execution of our trial. The primary analysis population for assessing the efficacy of the intervention will be a full analysis set (FAS), while the supplementary analysis population will be a PPS. The results of the FAS and PPS analyses will be compared and reflected in the efficacy evaluation. “Multiple Imputation” method will be used to obtain the missing value. All analyses will be performed at the 5% (two-sided) significance level using SAS^®^ version 9.4 (SAS institute. Inc., Cary, NC, USA) software. We will not perform interim analyses.

Baseline characteristics and variables will be compared between the two groups. Categorical data will be compared using the Fisher’s exact test or chi-square test, while continuous data will be compared using the Wilcoxon’s rank sum test or independent *t*-test.

The difference in responder proportions will be tested using the chi-square test or Fisher’s exact test. The degrees of changes in the VAS, EQ-5D-5L, and ODI scores at 3 days after the treatment ends and 8 weeks after the intervention ends, relative to the baseline score, between the groups will be evaluated using analysis of covariance with baseline scores as covariates. Within each group, changes in VAS, EQ-5D-5L, and ODI scores at each time will be analyzed using one-way analysis of variance and a paired *t*-test or Wilcoxon signed rank test. Sub-analyses will be performed according to each institution.

A safety assessment will be conducted for all SAEs and AEs that will occur during the trial period. The incidences of SAEs and AEs will be compared between the two groups using chi-square test or Fisher’s exact test. A comparative analysis will be carried out between the groups for participants who will be out of normal range for a clinical laboratory test.

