Considering the results of this study, 650 nm ILA is expected to show safety, clinically significant improvement, pain reduction, and improvement of functional limitation and quality of life in patients with NSCLBP. This is important for the clinical use of 650 nm ILA and development of optimal laser parameters for the treatment of NSCLBP.

This protocol has certain limitations. First, we will not use different treatment methods of LA for NSCLBP treatment. The factors that influence the efficacy of LA are selected acupoints, wavelength, and energy dose. Various treatment methods of LA differ according to wavelength, energy dose, and acupoints for treating NSCLBP (16–19, 38). Since 650 nm ILA parameters, including the wavelength, power, energy dose, and acupoints, used in our pilot study show significant pain reduction at the intervention endpoint, we adopted only the 650 nm ILA parameters used in our pilot study in this study. Thus, further studies should be conducted to investigate the optimal parameters. Second, since most participants in our pilot study had moderate pain at the baseline and the high dropout rate owing to pain increase during the study period in the case of patients with severe pain was concerning, our study will include only patients with moderate NSCLBP, not those with severe NSCLBP. Third, since the practitioner will operate the laser emitting device according to the treatment method of each group (650 ILA group, 20 mW power for 10 min; control group, 0 mW power for 10 min), we cannot adopt practitioner blinding. Therefore, we will adopt an assessor- and patient-blinded study design.

Nevertheless, the findings of this study would suggest clinical evidence concerning the safety and efficacy of 650 nm ILA for the management of NSCLBP, thereby establishing the basis for further investigation. It would contribute to increasing the availability of laser and promoting the development of optimal laser treatment method in the management of LBP.

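### Hypothesis 3 says the treatment is safe, but the only inferential method fixed for adverse events is a test of difference, and a non-significant result from it cannot support that hypothesis

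*Protocol article*

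**What the plan says.** The Aims section lists investigating the safety of 650 nm ILA as its third aim. The Hypothesis section turns this into a directional claim: "The 650 nm ILA would be a safe treatment for patients with NSCLBP". No acceptable rate, margin or other criterion is attached to it.

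The Adverse events section says: "The occurrence rate of SAEs and AEs will be compared between the two groups in the safety assessment". The Statistical analysis section names the method: "The incidences of SAEs and AEs will be compared between the two groups using chi-square test or Fisher’s exact test". It also sets one level throughout: "All analyses will be performed at the 5% (two-sided) significance level".

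The Sample size estimation section rests on efficacy only, "assuming an expected responder proportion of 30% in the control group and 60% in the 650 ILA group", with "a two-sided alpha level of 0.05, and a statistical power of 0.8". It makes no mention of AE rates.

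Two further elements of the safety assessment are stated. Each AE is recorded with causality, severity, timing and the measures taken, and participants with out-of-range laboratory values are compared between groups. The Discussion already describes the 650 nm ILA as safe, and says of the results: "650 nm ILA is expected to show safety, clinically significant improvement, pain reduction".

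**The concern.** Hypothesis 3 is a claim that harm is small or absent. The null hypothesis of a chi-square or Fisher test is that the two AE rates are equal. Rejecting that null with more events on ILA would be evidence against Hypothesis 3. Failing to reject it says only that the data did not separate the arms, which is the likely result in a small trial whether or not there is an excess. The stated test can therefore damage the stated hypothesis but cannot confirm it.

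Safety evidence is one of the trial's headline purposes, named in the Abstract, the Aims and the Discussion. If the result is a p-value above 0.05 with no interval, a reader cannot tell an excess that has been excluded from one that was never detectable. This matters most for SAEs and for uncommon individual AEs, where 53 per arm gives little information on a difference.

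**Working it through.** **Inputs from the article.** 1:1 allocation; 42 evaluable and 53 randomised per group; 20% dropout; two-sided alpha 0.05; chi-square or Fisher test. **Assumed, because the article gives no AE rate:** control rates from 1% to 15%, tripled on ILA. The article reports only that no AEs in its pilot were associated with laser irradiation.

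**1. The article's own sample size.** n = (1.96·√(2×0.45×0.55) + 0.842·√(0.30×0.70 + 0.60×0.40))² / 0.30² = 41.98, so 42 per group. Then 42 / (1 − 0.20) = 52.5, so 53 per group. Both figures reproduce. They concern responders only.

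**2. Power of the AE test.** For control rate p_c and ILA rate p_t, power = Σ Bin(a; 53, p_c) × Bin(b; 53, p_t), summed over all pairs (a, b) with b > a and p-value ≤ 0.05. The chi-square is uncorrected.

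| Control vs ILA | Fisher | Chi-square |
|---|---|---|
| 1% vs 3% | 0.3% | 4% |
| 3% vs 9% | 11% | 24% |
| 5% vs 15% | 27% | 41% |
| 10% vs 30% | 68% | 75% |
| 12% vs 36% | 79% | 85% |
| 15% vs 45% | 90% | 94% |

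With 42 per arm, 5% vs 15% gives 20% (Fisher) and 36% (chi-square). By the normal-approximation formula of step 1, 80% power would need 141 per arm at 5% vs 15% and 245 per arm at 3% vs 9%.

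**3. What a non-significant result can look like.**
- 0/53 vs 5/53: Fisher p = 0.057. Six events against none are needed for Fisher significance (p = 0.027). Four suffice for the uncorrected chi-square.
- 3/53 vs 9/53: Fisher p = 0.12, chi-square p = 0.066. The risk difference is 9/53 − 3/53 = 6/53 = 11.3 percentage points, with Newcombe 95% CI −1.1 to 24.1. The interval shows that a large excess remains possible; the p-value alone does not.

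**4. What zero events would exclude.** With 0 of 53, the upper limit of the two-sided exact 95% interval solves (1 − p)^53 = 0.025, so p = 1 − 0.025^(1/53) = 0.067. Zero SAEs on ILA would still be compatible with a true rate up to about 6.7%.

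**The case against.** The strongest reply is that the article states no such decision rule. It says that incidences will be compared, and it never links Hypothesis 3 to a p-value above 0.05. A reader might infer, from the lack of any other criterion and from the Discussion's expectation of safety, that non-significance will be declared as safety. The article does not say so, and an expectation voiced in a Discussion is not an analysis criterion. This part of the reply stands.

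Secondly, a reader might infer that a tripled AE rate would generally be missed. That is not supported either. It depends on a control rate the article does not give. From about 12% in the control arm the test has roughly 80% power or better, and repeated needling at several points in both arms could plausibly bring the rate of any AE into that range. A fourfold rate, 5% vs 20%, would be detected more often than not (55% Fisher, 67% chi-square). This also stands, and it confines the power concern to uncommon events and SAEs.

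Thirdly, the safety assessment is wider than one test. It includes recording of causality and severity, and a laboratory comparison. That is true, but neither is tied to a criterion for Hypothesis 3.

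Finally, comparing AE incidence with a Fisher or chi-square test is common practice, and intervals may be specified in a full protocol or analysis plan that is not shown. The absence of intervals from a condensed article is accordingly not the fault alleged. The point rests on two things the article does state, a hypothesis of safety and a test that cannot support it, and those would still need reconciling.

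**Conclusion.** The point holds as a mismatch between the stated hypothesis and the stated method. At any background rate, a non-significant test of difference is not evidence that the treatment is safe. How easily a real excess would be missed depends on assumed rates: for a tripled rate with all 53 per arm analysed, power is about 41% or less at a control rate of 5% or lower, and about 79% to 85% at 12%. For SAEs, if their rate is near 1%, the test is almost uninformative (0.3% to 4% power).

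Both arms are needled, so the between-arm comparison addresses the laser component only. Incidence in the ILA arm is what describes the safety of the procedure as a whole.

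This is a worthwhile, inexpensive correction. It does not affect the primary efficacy analysis.

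**What to change.** In the Statistical analysis section, beside the test or in its place, specify:

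- the number and percentage of participants with any AE and any SAE in each arm, with exact 95% confidence intervals;
- the between-arm risk difference with its 95% confidence interval;
- a sentence stating that a non-significant difference will not be taken as evidence of safety.

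Reword Hypothesis 3 as an estimation aim: the incidence of AEs and SAEs with 650 nm ILA will be estimated with its precision. The expected precision can be illustrated by noting that zero SAEs in 53 participants would still be compatible with a true rate up to about 6.7%.

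No additional data or participants are needed. The costs are a more cautious safety statement and a wording revision which, under the Quality control section, must be approved by the Ministry of Food and Drug Safety and by the review boards of both hospitals.

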### Confidentiality and data management

All documents will be classified and logged with identification codes, but the names will remain concealed.

All identification records will be kept confidential and will not be accessible without IRB approval. All data will be recorded in the electronic case report forms (eCRFs) by the CRC and checked by a investigator, who will not be involved in the execution of this trial. Electronic data will be securely stored in the eCRFs using the myTrial data management system (NIKOM, Republic of Korea). Data access will be protected by user name and password. The data manager will have online access to the all data, whereas institutions will have access only to data related to their own institution. The data manager and the statistician will have online access to the entire database. The data coordinating center in the Korea Institute of Oriental Medicine will be unaffiliated with the sponsor and devoid of competing interests. No access to the data will be granted to anyone not approved by the IRB. In addition, raw data will be stored for 3 years after the completion of the trial. Participants will voluntarily offer informed written consent for the dissemination of their personal information.

## Discussion

The efficacy of LA for musculoskeletal pain is majorly determined by the energy dosage applied (35). Energy penetration through the skin is affected by the scatter, reflection, and absorption of energy by skin structures. As the acupoints are thought to be located in the myofascial layer, the low energy transmission of non-invasive LA may not be fully effective in stimulating acupoints (15). However, the 650 nm wavelength ILA used in this study is safe and can compensate for the scatter, reflection, and absorption of light by the skin and enhance energy transmission, because the laser is emitted at the acupuncture needle’s tip after being placed beneath the skin. The design of this study, including the ILA intervention (i.e., treatment acupoint and laser wavelength), treatment schedules, outcome measurements, and sample size, is based on that of our previous pilot study (21). In our previous pilot clinical trial (21), 650 nm ILA at bilateral GB30, BL23, BL24, and BL25 showed significant improvement in the VAS and ODI scores at the intervention endpoint and ODI score at 4 weeks after the intervention ends, compared with sham laser in patients with NSCLBP. Therefore, BL23, BL24, BL25, and GB30 were selected for treatment acupoints and 650 nm for laser wavelength in this study.

The clinical assessments used in LBP trials are often highly subjective and correlate poorly with symptoms. The responder index could be sensitive to clinically meaningful treatment effects and could mitigate the placebo effect (27). The preliminary developed responder index for chronic low back pain was at least 30% improvement in pain, with an improvement of at least 30% in patient global assessment and no worsening in function (27). We adopted responder proportions (≥30% relief on the VAS without analgesics increase) used in a recent chronic LBP clinical trial as a primary outcome (28). Four core outcome domains for LBP trial are pain intensity, number of deaths, health-related quality of life, and physical functioning (36, 37). We used change in VAS scores to measure the pain intensity, ODI scores to measure the physical functioning, and EQ-5D-5L scores to evaluate the health-related quality of life.

Considering the results of this study, 650 nm ILA is expected to show safety, clinically significant improvement, pain reduction, and improvement of functional limitation and quality of life in patients with NSCLBP. This is important for the clinical use of 650 nm ILA and development of optimal laser parameters for the treatment of NSCLBP.

This protocol has certain limitations. First, we will not use different treatment methods of LA for NSCLBP treatment. The factors that influence the efficacy of LA are selected acupoints, wavelength, and energy dose. Various treatment methods of LA differ according to wavelength, energy dose, and acupoints for treating NSCLBP (16–19, 38). Since 650 nm ILA parameters, including the wavelength, power, energy dose, and acupoints, used in our pilot study show significant pain reduction at the intervention endpoint, we adopted only the 650 nm ILA parameters used in our pilot study in this study. Thus, further studies should be conducted to investigate the optimal parameters. Second, since most participants in our pilot study had moderate pain at the baseline and the high dropout rate owing to pain increase during the study period in the case of patients with severe pain was concerning, our study will include only patients with moderate NSCLBP, not those with severe NSCLBP. Third, since the practitioner will operate the laser emitting device according to the treatment method of each group (650 ILA group, 20 mW power for 10 min; control group, 0 mW power for 10 min), we cannot adopt practitioner blinding. Therefore, we will adopt an assessor- and patient-blinded study design.

Nevertheless, the findings of this study would suggest clinical evidence concerning the safety and efficacy of 650 nm ILA for the management of NSCLBP, thereby establishing the basis for further investigation. It would contribute to increasing the availability of laser and promoting the development of optimal laser treatment method in the management of LBP.

## Ethics statement

This protocol (version. 1.0) was approved by the Ministry of Food and Drug Safety (date: March 16, 2022; Medical Device Approval # 1322). It was approved by the IRB of Kyung Hee University Korean Medicine Hospital (date: April 22, 2022; approval No.: KOMCIRB 2022-03-004-001) and Dongshin University Gwangju Korean Medicine Hospital (date: March 22, 2022; approval No.: DSGOH-2022-002). Participants and their companions will be informed of the study purpose and risks. All participants will provide written informed consent prior to participation.
